### Statistical Analysis

To maximize statistical power, outcomes will be analyzed using mixed-effects linear models to leverage the collection of data on more than 2 time points and to facilitate the analysis of unbalanced data based on participant attrition. Participants will be included as random effects, with group and time included as fixed effects, to assess within- and between-group differences over time. Sensitivity analyses will be conducted by including baseline values in models or other data relative to potential confounders to account for nonrandom allocation. Linear models will be structured to assess within- and between-group differences over time (eg, the inclusion of resistance and HIIT exercise), establishing the rate of change of intervention and control and determining whether these rates are distinct. The suitability of the models will be established by assessing model residuals and transformations made if residuals are not normally distributed or homoscedastic. Uncertainty in parameter estimates will be quantified using the Satterthwaite approximation for *df* values or through bootstrapping procedures. To facilitate interpretation of the magnitude of change across different outcomes, analyses will be standardized relative to the baseline SD, thus placing outcomes on a unitless scale. Principal component analysis will be conducted on change scores to investigate the clustering of outcomes relative to the magnitude of change.

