### Primary Outcome Measures

#### Occupational Physical Performance Overview

Occupational physical performance will be measured at weeks 12 and 24 using the Role Fitness Test (Entry), which is used by the British Army as a selection standard to confirm the appropriate level of fitness to commence basic training. It involves an isometric mid-thigh pull, seated medicine ball throw, and a timed 2-km run. A vertical jump test will be completed as a military-relevant field-based measure of power. The occupational physical performance tests will be conducted using military equipment and following military procedures (field-expedient measures). As part of military physical performance testing, there is a minimum standard that individuals must achieve, and maximum scores or values are used across these tests. The maximum values will be reported for the occupational physical performance tests in this study.

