### Secondary Outcome Measures

#### Pelvic Organ Prolapse

Pelvic organ prolapse will be measured by a pelvic health physiotherapist at weeks 6, 12, and 24. Vaginal examination will assess for prolapse using the Pelvic Organ Prolapse Quantification system (POP-Q) [39,40], quantifying pelvic support in stages from 0 to 4, with 0 indicating no prolapse demonstrated and 4 demonstrating full procidentia. A total of 6 defined points (Aa, Ba, C, D, Ap, and Bp) and 3 landmarks (genital hiatus, total vaginal length, and perineal body) will be measured using a *POP-Stix* (POPstix) tool. The hymen will be the fixed point of reference throughout the completion of the POP-Q. Each measurement will be taken in centimeters above or proximal to the hymen (positive number), with the plane of the hymen defined as 0 (Table 8) [39]. All measurements, except for total vaginal length, will be performed with maximal Valsalva. The POP-Q staging criteria are listed in Table 9 [39].

**Table 8 table8:** Description of the 9 measures of the Pelvic Organ Prolapse Quantification system.^a^

Points	Description	Range of values
Aa	Anterior vaginal wall 3 cm proximal to the hymen	−3 to +3 cm
Ba	Most distal position of the remaining upper anterior vaginal wall	−3 cm to +tvl
C	Most distal edge of cervix or vaginal cuff scar	N/A^b^
D	Posterior fornix	N/A
Ap	Posterior vaginal wall 3 cm proximal to the hymen	−3 to +3 cm
Bp	Most distal position of the remaining upper posterior vaginal wall	−3 cm to +tvl
gh^c^	Measured from middle of external urethral meatus to posterior midline hymen	N/A
pb^d^	Measured from posterior margin of gh to middle of anal opening	N/A
tvl^e^	Depth of vagina when point D or C is reduced to normal position	N/A

^a^Adapted from Bump et al [39].

^b^N/A: not applicable.

^c^gh: genital hiatus.

^d^pb: perineal body.

^e^tvl: total vaginal length.

**Table 9 table9:** Pelvic Organ Prolapse Quantification system staging criteria.^a^

Stage	Description
0	Aa, Ap, Ba, Bp=−3 cm and C or D≤−(tvl^b^ − 2) cm
1	Stage 0 criteria not met and leading edge <−1 cm
2	Leading edge≥−1 cm but ≤+1 cm
3	Leading edge>+1 cm but <+(tvl − 2) cm
4	Leading edge≥+(tvl − 2) cm

^a^Adapted from Bump et al [39].

^b^tvl: total vaginal length.

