#### Pelvic Floor Strength

Pelvic floor strength will be measured by a pelvic health physiotherapist at weeks 6, 12, and 24 using the PERFECT (power, endurance, repetitions, fast, every contraction timed) scheme [41]. The participant will perform maximum-effort pelvic floor contraction following instructions and a practice attempt. Power will be recorded on a modified Oxford scale of 0 to 5. Endurance will be assessed by counting the number of seconds until maximum voluntary contraction can no longer be sustained and fatigue is reached. Repetitions of this sustained contraction will be performed with a 4-second rest between each contraction. Fast contractions will be performed by 1-second maximum voluntary pelvic floor contraction and 1-second relaxation until a maximum voluntary contraction can no longer be achieved. Overactivity, coordination, and relaxation of the pelvic floor muscle contraction will also be assessed during the digital vaginal examination.

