##### Muscle Mass Analyses Using D3-Creatine

Whole-body muscle mass will be estimated using urinary D_3_-creatine at weeks 6, 12, 18, and 24 post partum (Figure 5). A single urine sample will be collected before ingestion of approximately 30 (SD 0.1) mg of D_3_-creatine tracer (D_3_-creatine, CK Isotopes) dissolved in approximately 50 mL of water. Participants will then collect all urine samples for 24 hours, starting immediately after tracer ingestion. A single urine sample will be collected 48 hours after tracer ingestion. The volume of urine collected over 24 hours will be recorded. Approximately 3 mL of each urine sample will be transferred to Eppendorf tubes and stored at −80 °C for later analysis.

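### The comparison of the groups' rates of change, read plainly, allows each woman her own level but not her own slope, so secondary outcomes with three or four visits get standard errors that are too small if women's rates differ

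*Protocol article*

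**What the plan says.** Statistical Analysis describes the model in one sentence: "Participants will be included as random effects, with group and time included as fixed effects, to assess within- and between-group differences over time". The abstract's Methods paragraph says the same. The stated purpose includes "establishing the rate of change of intervention and control and determining whether these rates are distinct". No participant-level slope for time and no other within-woman covariance is named.

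On inference the section says "Uncertainty in parameter estimates will be quantified using the Satterthwaite approximation for" degrees of freedom, or alternatively bootstrapping, with no resampling unit given. On model checking it says "The suitability of the models will be established by assessing model residuals and transformations made if residuals are not normally distributed or homoscedastic".

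The number of visits differs by outcome:

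- **Two visits:** the primary performance tests (weeks 12 and 24), DXA and tibial CT (weeks 6 and 24), and D3-3MH muscle protein breakdown (weeks 12 and 18).
- **Three visits (weeks 6, 12 and 24):** POP-Q ("Pelvic organ prolapse will be measured by a pelvic health physiotherapist at weeks 6, 12, and 24"), PERFECT ("Pelvic floor strength will be measured by a pelvic health physiotherapist at weeks 6, 12, and 24"), the musculoskeletal physiotherapy assessment, PFDI-20, ICIQ-VS, WHOQOL-BREF, EPDS, patellar tendon properties and muscle architecture.
- **Four visits:** only muscle mass, from "urinary D_3_-creatine at weeks 6, 12, 18, and 24 post partum".

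**The concern.** The question asked is whether mean slopes differ between groups. A random intercept gives each woman her own level but treats all women in a group as changing at one common rate, with only visit-to-visit noise around it. If true rates differ, that variation is averaged into the within-woman residual, and the degrees of freedom count visits rather than women. The estimated standard error of the slope difference is then too small.

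Satterthwaite degrees of freedom do not repair this, because the variance itself is wrong. The residual checks might hint at it, but the response they name, a transformation, does not change the within-woman covariance.

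The article gives reasons to expect some variation in rates. Control women may exercise as they choose. The home-based programme is not routinely supervised and can be modified to the individual. Compliance is expected to vary. A principal component analysis of change scores is also planned.

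At stake are the intervals and p-values for the pelvic, psychological, tendon and muscle outcomes, for which the Hypothesis section predicts greater improvement with training.

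**Working it through.** The plan states no figure on this point, so there is none to reproduce.

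**Inputs from the article.** Visits at weeks (6, 12, 24) or (6, 12, 18, 24); n = 15 per group (recruitment target) or 11 (before allowance for dropout); α = .05, taken as two-sided.

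**Assumption.** k = SD of the true 18-week change ÷ residual SD, shown from 0 to 2. With τ the SD of the weekly slope and σ the residual SD, k = 18τ/σ, so τ²/σ² = k²/324.

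**Step 1: spread of visit times,** S = Σ(t − mean)².

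- Three visits (mean 14): 64 + 4 + 100 = 168.
- Four visits (mean 15): 81 + 9 + 9 + 81 = 180.

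**Step 2: true variance of the difference in mean slopes.** (2/n)(τ² + σ²/S) = (2σ²/nS)·A, where A = 1 + S·k²/324.

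**Step 3: variance the random-intercept model reports.** On average (2σ²/nS)·E, where, for m visits and complete data,

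E = [2n(m−2) + (2n−2)A] / [2n(m−1) − 2].

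The ratio of reported to true standard error is √(E/A).

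Example, n = 15, three visits, k = 2: A = 1 + 168×4/324 = 3.074; E = (30 + 28×3.074)/58 = 2.001; ratio = √(2.001/3.074) = 0.807.

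Example, n = 15, four visits, k = 2: A = 1 + 180×4/324 = 3.222; E = (60 + 28×3.222)/88 = 1.707; ratio = √(1.707/3.222) = 0.728.

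**Step 4: type I error with equal mean slopes.** The squared test statistic is A·χ²(1) divided by [A·χ²(2n−2) + χ²(2n(m−2))]/df, with df = 2n(m−1) − 2. It is compared with the squared two-sided 5% t value on df. I used 2,000,000 draws per cell. Results for n = 15:

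| k | SE ratio, 3 visits | Error, 3 visits | SE ratio, 4 visits | Error, 4 visits |
|---|---|---|---|---|
| 0 | 1.00 | 5.0% | 1.00 | 5.0% |
| 0.5 | 0.97 | 5.7% | 0.96 | 6.1% |
| 1 | 0.91 | 7.5% | 0.87 | 8.8% |
| 2 | 0.81 | 11.3% | 0.73 | 15.3% |

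With 11 per group the k = 2 values are 11.4% and 15.4%. The normal approximation 2[1 − Φ(1.96 × ratio)] agrees: 1.96×0.807 = 1.58 gives 11.4%, and 1.96×0.728 = 1.43 gives 15.4%. With three visits the variance ratio A/E cannot go much above 2, so the limiting error is about 2[1 − Φ(1.96/√2)] = 16.6%.

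**Step 5: time as a category.** With time as a factor but still only a random intercept, the week 24 minus week 6 contrast at k = 2 has error 10.5% (three visits) and 13.5% (four visits) in 20,000 simulated trials. Making time categorical does not by itself cure the problem.

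**Step 6: two visits.** With m = 2, E = (2n−2)A/(2n−2) = A, so the ratio is exactly 1. The test equals a t test on change scores and is valid at every k.

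**Step 7: with slopes allowed to vary.** Testing each woman's own slope, which for complete data corresponds to a random-slope analysis, gives error between 4.5% and 5.3% in every simulated scenario.

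**Step 8: how often a random slope collapses.** With complete data, the moment estimate of slope variance is zero or negative when F(2n−2, 2n(m−2)) < 1/A. For three visits and n = 15 this is about 37% of data sets at k = 0.5 (1/A = 0.885) and 13% at k = 1 (1/A = 0.659). With n = 11 it is 39% and 18%.

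**The case against.** The strongest reply is that the article never says intercept only. A random-slope model also has time as a fixed effect, so listing time there does not exclude a slope. The detail of within-person covariance is usually left to an analysis plan, which is not shown, and the article is a condensed text. This stands in part. A reader might infer that the plan fixes participants as the sole random term and rules out slopes, but the text supports only a plain reading to that effect. Incomplete specification alone would be no finding. What remains is that the article assigns participants to the random part and time to the fixed part, asks this model to compare rates, and names no step that would correct the result.

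A reader might also infer that the standard errors are simply too small. That is conditional. At k = 0 they are correct and at k = 0.5 the shortfall is 3 to 4%. The article's remarks on free exercise and individual modification make k = 0 unlikely but do not locate k.

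The bootstrap alternative stands as a partial answer: resampling whole women would largely avoid the problem, but the article does not say what is resampled.

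Finally, the remedy is not free. At this sample size a random slope often collapses to zero variance when k is small, and a comparison of per-woman slopes deals less well with the unbalanced data that the mixed model was chosen to handle.

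**Conclusion.** The concern holds in conditional form, for secondary outcomes only. Under a random intercept alone, the standard error of the rate comparison is 9% (three visits) to 13% (four visits) too small at k = 1, and 19% to 27% too small at k = 2. Type I error is then 7.5% to 8.8%, and 11.3% to 15.3%. The four-visit figures apply to one outcome, D3-creatine muscle mass, and should not be read across to the rest.

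It would be wrong to conclude that the primary result is at risk. The performance tests have two visits, for which the test is valid. The sample size is also untouched, since it comes from a two-group comparison of post-training means and not from the mixed model.

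The figures rest on the plain reading of the random part, linear individual change, complete data, two-sided testing and an assumed k.

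**What to change.** For outcomes with three or more visits, state the within-woman structure in the Statistical Analysis section. The better default is time as a factor, with group-by-time, an unstructured within-woman covariance and Kenward-Roger degrees of freedom. The covariance needs 3×4/2 = 6 parameters for three visits and 4×5/2 = 10 for four. The rate question can then be answered by a linear contrast of the visit means. The alternative is a by-participant random slope for time in addition to the intercept. If bootstrapping is used, say that whole women are resampled within group. A comparison of per-woman slopes should be only a fallback if the model cannot be fitted, because it handles incomplete visits less well. If a fuller plan already specifies this, the article's wording need only be aligned with it.

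The cost is a sentence or two of analysis text and no new data. Intervals for these outcomes will be somewhat wider. With 11 to 15 women per group, a random-slope fit will often return zero slope variance when true variation is small, which is why the unstructured covariance is preferred.

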### Ethical Considerations and Consent

This study received ethical approval from the Ministry of Defence Research Ethics Committee (942/MODREC/18) in April 2019. Participants will be provided with an information sheet at least 24 hours before consenting to participation and given a verbal description of the study. Written informed consent will be obtained at the start of the first testing session. Adverse events and reactions will be reported to the trial committee and considered by a minimum of 3 trial committee members.

### Confidentiality and Data Storage

All data will be handled in accordance with the project’s data management plan and in compliance with the General Data Protection Regulation. All raw data will be pseudonymized during the trial. Anonymized data will be uploaded to the active research data storage system at Nottingham Trent University for a minimum of ten years following the completion of the study. Data access rights will be provided only to the relevant members of the research team.

## Results

This study was funded by the Ministry of Defence in March 2018, awarded by BAE Systems (Operations) Limited, contracted through CORDA business (Award Task 0157 proposal reference ASC\CMRCL\RFQ\00694). The study received ethical approval from the Ministry of Defence Research Ethics Committee (942/MODREC/18) in April 2019. Data collection initially started in July 2019, and in March 2020, a total of 4 participants (2 intervention and 2 control) had completed all testing sessions. The study was paused in March 2020 because of the COVID-19 pandemic, but recruitment restarted in May 2021. The study is expected to conclude in September 2022 and the results will be made available thereafter.

## Discussion

### Hypothesis

We hypothesize that occupational physical performance will improve to a greater extent in the training group, who will receive the combined core reconnection and physical development training intervention, than it will in the control group. We also hypothesize that the training group will see greater improvements in all the secondary outcome measures.

### Limitations

Nonrandom allocation could influence participant bias, but it was deemed necessary to use the approach of geographical separation of participants to limit the likelihood of the intervention being shared between the training and control groups. It was deemed unethical for the control group to act as a *true control* (ie, to limit control participants’ physical activity and exercise patterns and levels), and as such, the participants can complete whatever exercise they choose during the study period. Exercise logs will be used to monitor the exercise conducted by the control group, allowing the comparison of any exercise completed between both groups. In addition, it will not be possible for the research team to be blinded to participant group allocation, as the research associates will be involved in both the testing and training of all study participants.

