#### Bone Density and Morphology

A 3D high-resolution peripheral quantitative computed tomography system (XtremeCT II, Scanco Medical AG) will be used to assess volumetric bone mineral density (vBMD), geometry, microarchitecture, and estimated mechanical strength of the nondominant (self-reported) tibia at 6 and 24 weeks post partum. A 3D representation of approximately 10 mm of the tibia in the axial direction, at both the metaphyseal (4% site) and diaphyseal (30% site) tibia, will be obtained from 165 computed tomography slices with an isotropic voxel size of 61 μm. Tibial length will be measured before the first scan, taken as the distance between the medial malleolus and the tibial end plate. The leg of each participant will be fitted into a carbon fiber shell and immobilized within the gantry of the scanner for the duration of the scan. A reference line will be placed at the tibial end plate, with the first computed tomography slice taken at 4% and 30% of the tibial length from the reference line for the metaphyseal and diaphyseal tibia. For follow-up measurements at the 4% site, automatic algorithms will match the volumes of interest to baseline scans, using the cross-sectional area (CSA) within the periosteal boundary, so only the bone volume common to the baseline scans will be assessed [48]. The matching algorithms will be disabled for analysis at the 30% site [49]. Daily quality control scans will be performed using a phantom containing hydroxyapatite (HA) rods. The quality of each high-resolution peripheral quantitative computed tomography scan will be reviewed according to the manufacturer’s visual grading system, and poor-quality scans will be excluded. Data processing will be performed as per Boutroy et al [48] and Burghardt et al [50]. The manufacturer’s standard evaluation procedure will be used to derive the following outcomes: total vBMD (mg HA∙cm^3^), trabecular vBMD (mg HA∙cm^3^), cortical vBMD (mg HA∙cm^3^), trabecular bone volume fraction (%), trabecular area (mm^2^), cortical area (mm^2^), cortical thickness (mm), trabecular thickness (mm), trabecular number (mm^−1^), trabecular separation (mm), cortical porosity (%), and cortical pore diameter (mm). The biomechanical properties under uniaxial compression, specifically stiffness (kN/mm) and failure load (kN), will be determined by micro–finite element analysis [51]. Evaluations will be performed by the same researcher to ensure consistency of periosteal and endosteal contouring. The coefficient of variation at the 4% site is 0.2% for total vBMD, 0.4% for trabecular vBMD, 0.9% for cortical vBMD, ≤1.3% for geometry, ≤2.1% for trabecular microarchitecture, 7.8% for cortical porosity, and ≤3.2% for stiffness and failure load [52]. The coefficient of variation at the 30% site is 0.3% for total vBMD, 0.2% for cortical vBMD, ≤0.8% for geometry, 4.9% for cortical porosity, and ≤0.7% for stiffness and failure load [52].

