
#### Patellar Tendon Properties

##### Overview

Measures of patellar tendon biomechanical properties will be obtained in vivo during voluntary isometric ramped contractions [53] at 6, 12, and 24 weeks post partum. All measurements on the dominant limb will be performed by the same researcher.

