##### Patellar Tendon Length and CSA

Resting patellar tendon length and patellar tendon CSA will be measured using real-time B-mode ultrasonography at a fixed 90° knee angle. The distance between the apex of the patella and the tibial tuberosity, recorded using sagittal ultrasound images, will be taken as resting patellar tendon length. Patellar tendon CSA will be measured using the ultrasound probe placed in the transverse plane, and images will be captured at 25%, 50%, and 75% of tendon length. Images will be analyzed offline using ImageJ (v1.50c; National Institute of Health), 3 images will be averaged at each site, and the mean will be used for calculating tendon stress.

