#### Muscle Architecture

The muscle architecture of the *m. vastus lateralis* will be assessed at 6, 12, and 24 weeks post partum by the acquisition and analysis of B-mode ultrasonography (MyLab Omega, Esaote) images with a 4- to 15-MHz linear array probe, with the participant lying supine. Images of the dominant leg will be taken at 50% of the length of the and at the midsagittal line of the *m. vastus lateralis*. The scan site will be marked and traced onto acetate with reference points for subsequent tests. The transducer will be aligned to the fascicle plane to allow optimal capture of the fascicles [56]. Muscle thickness, fascicle length, and pennation angle will be assessed using digitizing software (ImageJ v1.50c). Muscle thickness will be measured as the distance between the superficial and deep aponeuroses of the *m. vastus lateralis*. Muscle thickness values will be calculated as the mean of measurements taken at the proximal, central, and distal locations on the captured ultrasound image. The visible portion of the fascicle within the scan window will be measured. The nonvisible portion of the fascicle will be estimated by linear extrapolation of the fascicles and aponeuroses. The linear extrapolation method is a valid technique for measuring vastus lateralis fascicle length [57], and to reduce fascicle extrapolation error (reported as approximately 4% [58]), an average of 3 fascicles across the image will be taken. The pennation angle will be determined as the angle created from the visible insertion of the fascicle into the deep aponeurosis. An average of 3 pennation angles will be taken across the image.

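### The Limitations section rules out blinding for the whole research team, but its reason covers only live contact, and stored ultrasound and bone images could be read under masked codes

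*Protocol article*

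**What the plan says.** The Limitations section of the protocol article states that "it will not be possible for the research team to be blinded to participant group allocation". It excepts no role and no outcome. The one reason it gives is the double role of the staff, who test as well as train.

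The Methods describe three groups of secondary outcomes that are read from images:

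- **Patellar tendon length and cross-sectional area.** "Images will be analyzed offline using ImageJ". The area then enters the calculation of tendon stress and Young modulus. The overview of the tendon section adds: "All measurements on the dominant limb will be performed by the same researcher".
- **Vastus lateralis architecture.** "Muscle thickness, fascicle length, and pennation angle will be assessed using digitizing software (ImageJ v1.50c"). Three fascicles and three angles are averaged per image, and the part of each fascicle outside the scan window is extrapolated.
- **Tibial bone by high-resolution peripheral quantitative CT.** "Evaluations will be performed by the same researcher to ensure consistency of periosteal and endosteal contouring". Each scan is graded visually on the manufacturer's system, and "poor-quality scans will be excluded".

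On coding, the section on confidentiality and data storage says: "All raw data will be pseudonymized during the trial". The article describes no masked reading, grading or exclusion for any image.

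**The concern.** The statement is wider than its reason. Someone who has trained or tested a participant cannot be blinded to her group in the laboratory. The same person, or a colleague, can still be blinded to which participant a stored image belongs to.

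Image reading here leaves room for judgement: which fascicles and angles to measure, where to extrapolate, how to contour, and which scans to discard. The Hypothesis section predicts greater improvement with training in all secondary outcomes, so a reader who knows the group also knows the expected direction. Allocation is nonrandom, by location of care, so avoidable detection bias would add to possible confounding. The planned minimum is 15 recruited per group, so a few shifted readings or discarded scans can move a group mean. Outcomes are also to be standardized, and principal component analysis run on change scores, so a reading bias in several image outcomes could carry into the cross-outcome summary.

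**Working it through.** The article states no figure on this point, so there is none to reproduce. The check sets the reason for not blinding against the way each outcome is obtained.

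**1. What the reason covers.** The reason is that the same staff test and train. It applies wherever staff meet participants. It is also loosely worded: it speaks of training all participants, whereas the Intervention overview says that controls are not prescribed exercise.

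**2. Where each outcome stands.**

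| Outcome | How obtained | Does the reason apply? |
|---|---|---|
| Primary: mid-thigh pull, medicine ball throw, 2-km run, vertical jump | Live test | Yes |
| Prolapse staging, pelvic floor strength, rectus diastasis | Hands-on examination | Live contact; masked file codes cannot help |
| Acquisition of ultrasound and CT images | Live | Yes |
| Tendon length and area: reading | From images; offline stated explicitly | No |
| Muscle architecture: reading | Digitized from captured images; later reading inferred from the software described | No |
| Tibial CT: evaluation and quality grading | Evaluation of acquired scans by one researcher; later reading inferred | No |

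**3. Whether existing coding already masks the reader.** Pseudonymized data carry a study code in place of a name. One researcher performs all the tendon measurements and may know the codes of the women measured. Pseudonyms therefore do not ensure masking. New codes held by someone other than the reader would be needed.

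**4. Whether masking is technically possible.** Tibial follow-up scans at the 4% site are matched to baseline by automatic algorithms, so visit order may have to stay visible there. Matching is disabled at the 30% site, so visit can be hidden. Group can be hidden at both sites.

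**5. Volume of files**, at the planned minimum of 2 × 15 = 30 women:

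- Ultrasound sessions at weeks 6, 12 and 24: 30 × 3 = 90.
- Tendon area images: 3 positions × 3 images = 9 per visit, so 9 × 90 = 810.
- Tibial scans at weeks 6 and 24, two sites: 30 × 2 × 2 = 120.

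Tendon length, tendon elongation and muscle files come on top. This is a batch task, but not a trivial one.

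**The case against.** The strongest reply is that the article condenses a fuller protocol. How image files are labelled is the kind of detail left to that document or to laboratory procedures, and the lack of blinding is openly disclosed. Part of this stands. A reader might infer that all images will be read with knowledge of group. The article does not say so: it does not name who digitizes the muscle images or how files are labelled, and it does say that raw data are pseudonymized. What remains is that the article makes a positive, unqualified statement that blinding is impossible, and its own Methods show that this is too broad for part of the outcome set.

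Three further inferences are tempting and unsupported:

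- **That bone contours are drawn by hand.** The article says that the manufacturer's standard evaluation is used and does not state how much manual input there is. It does treat contouring as operator-dependent, since one researcher is assigned for consistency.
- **That the reported fascicle extrapolation error of about 4% measures the possible bias.** It is an extrapolation error for one outcome, taken from a cited source and already reduced by averaging three fascicles. It is not a difference between groups caused by knowing the group. Nor do the coefficients of variation given for volumetric bone density (0.2% to 0.9% at the 4% site, 0.2% to 0.3% at the 30% site) settle the matter the other way, because they describe repeatability and not bias.
- **That masked reading would blind the outcome assessment of the trial.** It would protect one step of some secondary outcomes. Probe placement, scan-site placement and participant effort would remain unmasked.

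**Conclusion.** The point holds in a limited form. The declaration in the Limitations section should not extend to the reading of stored images, because its reason does not reach that step and the article provides no masking for it. The outcomes concerned are tendon dimensions and the stress and modulus derived from them, muscle architecture, and tibial CT measures, including which scans are excluded.

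No numerical size can be given: the document contains no estimate of reader bias and no expected change for these outcomes. Power, sample size and error rates are unaffected. The conclusion assumes that muscle and bone images, like tendon images, are read after the visit, which the described software evaluation implies without stating it. It is a cheap improvement and not a flaw that endangers the main comparison.

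**What to change.** Limit the blinding statement to staff who conduct live testing or training, and add wording such as:

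*Stored ultrasound and tibial CT files will be relabelled with new random codes by a team member other than the reader. The codes will hide participant and group, and also visit except where matching to baseline at the 4% site requires it. Quality grading, exclusion and digitizing will be done under these codes. The codes will be opened only after all readings are locked.*

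Because groups are defined by location of care, labels that reveal location should be removed as well.

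**Cost.** Existing staff would handle the files, hold the key and apply a lock step; the document gives no basis for an estimate in hours. Images from the 4 participants who had completed all sessions by March 2020 may need a second reading if they have already been digitized. Masking will be incomplete where a reader recognises an image or where visit order must stay visible.
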